### Outcome measures

2.8.

#### Primary outcome measures

2.8.1.

The primary outcome measures are PTSD symptom severity and number of participants with probable PTSD according to a PCL-5 cut-off of 33, which showed the best sensitivity-to-specificity-ratio for detecting PTSD (Weathers et al., 2013). Due to the online-design, we could not use CAPS interview as Pigeon et al. (2022) did to survey PTSD symptom development and decided to use PTSD Checklist for DSM-5 (PCL-5; Weathers et al., 2013) and Post-traumatic Cognitions Inventory (PCTI; Foa et al., 1999) as self-reports instead, both applied at T0, T1 and T2. Whereas the PCL-5 covers all PTSD symptoms, PTCI specifically measures trauma-related cognitions. The PCL-5 asks respondents to rate bothering of PTSD symptoms during the past month on a 5-point likert scale (1 = not at all to 5 = extremely) and has strong internal consistency (*α* = .94), test–retest reliability (*r* = .82), and convergent (*rs* = .74 to .85) and discriminant (*rs* = .31 to .60) validity (Blevins et al., 2015). The PTCI consists of 33 questions about trauma-related cognitions (based on the three factors Negative Cognitions About Self, Negative Cognitions About the World and Self-blame) which respondents rate on a 7-point-likert scale (absolutely no consent to strong consent). As PCL-5, PTCI shows excellent psychometric properties with internal consistency ranging from *α* = of .86–.97 (Foa et al., 1999). As the PCL-5 contains the item ‘Trouble falling or staying asleep?’ (Weathers et al., 2013), all analyses for the PCL-5 will be conducted with and without this item separately to detect whether potential changes on this measurement are solely driven by changes in sleep quality.

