### Sample size

2.4.

The planned sample size is based on calculations in G*Power 3.1.9.7 (Faul et al., 2007). Literature investigating the effect of combined sleep- and trauma-focused therapy on trauma-related symptoms is scarce. Pigeon et al. (2022) report a medium sized effect of CBT-I on trauma-related symptoms measured with the Clinician Administered PTSD Scale (CAPS; Blake et al., 1995) in individuals diagnosed with PTSD after having experienced a traumatic event within the past year. Referring to this finding and being interested in a clinically relevant effect, we chose an effect size of Cohen's *f* = .25 as a basis for power analysis and sample size calculation. Calculations setting the desired power to 80% and the risk of Type I error rate to *α* = 5% resulted in a required sample size of *N* = 86 to be able to detect medium sized between factor effects in a mixed design, provided the assumed effects exists in the investigated population. Considering a dropout rate of 20% from guideline-recommended psychological treatments for post-traumatic stress disorder (Varker et al., 2021) as an orientation for potential attrition rate, we intend to recruit *N* = 52 participants per group. Due to the exploratory nature of this pilot study, we used only our primary outcome measure for sample size calculations.

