### Statistical analysis

2.9.

Statistical analyses will be based on a mixed general linear model design with the two-level between group factor intervention (intervention vs. control group) and the three-level within group factor time (assessments at T0, T1 and T2) for primary and secondary outcome measures to account for both hypotheses tested in this study. A multilevel approach including study centers with their, presumably, differing TAU interventions, is not feasible due to too low a number of study centers at this hierarchical level. However, as discussed below, study centre and TAU interventions will be used as covariates and for exploratory analyses. For the first research question, the interaction between groups and time will be analysed to determine whether PTSD symptom severity differs for the intervention group after receiving the add-on treatment. For the second research questions, sleep disturbance before the intervention will be used to predict PTSD symptom severity at first and second follow-up for both groups. Due to the exploratory nature of this study, analysis will be conducted both with an intention-to-treat and a per-protocol approach, allowing for a comparison of both effect estimates (Gupta, 2011). For intention-to-treat analysis, dropouts will be included with a last observation carried forward strategy. Extreme cases and outliers will be checked for validity and excluded for per-protocol analysis if indicated. Dropouts will be reported with time point and reason in the final results. We intend to include age, gender, severity of trauma (indicated by classification in type-1 and -2 traumata), number of previous traumatic events, content of trauma-related outpatient treatment sessions and recruiting centre as covariates and in further exploratory analyses. Despite our efforts to proactively reduce variance in trauma treatment among participating trauma centers by organizing joint supervisions, we assume there will be left some significant variance that has to be considered in the statistical analyses. The content of trauma-related outpatient treatment sessions will be classified into trauma-focused versus non-trauma-focused therapy elements since it has been shown that in symptomatic acutely traumatized individuals this may cause a significant difference in treatment outcome (Roberts et al., 2019). Furthermore, we will survey whether sleep interventions have been included in the therapy process or not. By this, we intend to control for the most relevant confounding factors arising from between-participant-treatment-differences.

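### Two primary outcomes are left unranked while the sample size rests on one unnamed primary, and the yes/no outcome is put into a linear model whose T0 level carries almost no information

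*Protocol article*

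**What the plan says.** - **Primary outcomes (Section 2.8.1).** "The primary outcome measures are PTSD symptom severity and number of participants with probable PTSD according to a PCL-5 cut-off of 33". Neither is placed above the other. The same paragraph then introduces the PCL-5 and the PTCI "as self-reports instead, both applied at T0, T1 and T2". It does not say whether the PTCI is itself a primary outcome or only a supporting instrument.
- **Sample size (Section 2.4).** The text says "we chose an effect size of Cohen's *f* = .25 as a basis for power analysis and sample size calculation", "setting the desired power to 80% and the risk of Type I error rate to *α* = 5" per cent, and arrives at N = 86 for a between-factor effect in a mixed design. It adds that "we used only our primary outcome measure for sample size calculations". The outcome is in the singular and is not named. The same sentence calls the trial an exploratory pilot.
- **Model (Section 2.9).** "Statistical analyses will be based on a mixed general linear model design with the two-level between group factor intervention", with time at T0, T1 and T2, for primary and secondary outcomes alike. No other method is given for the yes/no outcome. The group-by-time test for the first research question is worded for symptom severity only.
- **Repeat analyses.** In Section 2.8.1, "all analyses for the PCL-5 will be conducted with and without this item separately". In Section 2.9, "analysis will be conducted both with an intention-to-treat and a per-protocol approach". Neither version is named as the main one in either case.
- **Entry and T0 (Sections 2.3 and 2.7).** Entry requires a PCL-5 above 33, the value that also defines probable PTSD. The T0 questionnaire is a separate administration after screening, consent and randomization.

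**The concern.** Sections 2.4 and 2.8.1 do not fit together. One outcome receives the full 5%, but at least two are called primary and no rule says what counts as success. A positive finding on severity alone, or on case numbers alone, could each be reported as the primary result. The 5% stated in Section 2.4 would then not be the error rate of the claim.

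The second part concerns the binary outcome. Lowering the risk of developing PTSD is a headline aim, yet the only method offered for the number of cases is a linear model of 0/1 values over three visits. At the first of those visits nearly everyone is a case because of the entry rule. No power is given for this outcome.

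**Working it through.** **1. The plan's own figure.** Inputs: f = 0.25, alpha 0.05 and power 80% (Section 2.4); two groups; m = 3 visits (Section 2.9). The correlation between visits is not given; ρ = 0.5 is assumed. For the between-factor F test:

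λ = N·m·f² / (1 + (m − 1)ρ) = 86 × 3 × 0.0625 / (1 + 2 × 0.5) = 16.125 / 2 = 8.06, with 1 and 84 degrees of freedom.

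The power is 0.801, and N = 86 is the smallest even number that reaches 80%. The stated figure is reproduced, and it uses the whole 5% on one test of one outcome.

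**2. Family-wise error if any one primary suffices.** For independent tests:

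- two primaries: 1 − 0.95² = 9.75%
- three primaries: 1 − 0.95³ = 14.3%

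The outcomes are correlated, so the group-by-time test was simulated under no group effect, with 20,000 trials per scenario. Assumptions:

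- N = 86 or 104
- visit correlation 0.5 or 0.7
- about 33% or 54–55% at or above the cut-off after baseline
- PTCI correlated about 0.6 with PCL-5
- T0 either all above 33, or re-measured with correlation 0.82 to screening (the PCL-5 test–retest figure in Section 2.8.1)

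| Test | Rejection rate |
|---|---|
| Yes/no outcome alone, uncorrected | 4.8–5.3% |
| Yes/no outcome alone, Greenhouse–Geisser | 4.7–5.1% |
| Severity or yes/no outcome | 8.5–9.4% |
| Any of three, PTCI included | 11.8–12.6% (12.7% in a separate run) |

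The excess comes from having several primaries, not from the linear model on 0/1 data.

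**3. The T0 level of the yes/no outcome.** If the screening score served as T0, 100% would be cases in both arms. With T0 re-measured as above, about 95% are. In both settings T0 adds almost nothing to a comparison of arms.

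**4. Power for the yes/no outcome.** The documents give no case rates, so a range is assumed. With n = 86 / 2 = 43 per arm, two-sided 5% and p̄ the mean of the two rates:

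power = Φ{ [ |p₁ − p₂| − 1.96·√(2p̄(1 − p̄)/n) ] / √([p₁(1 − p₁) + p₂(1 − p₂)]/n) }

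For 50% vs 30%: (0.200 − 1.96 × 0.1057) / 0.1034 = −0.07, so power is 47%.

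| Assumed case rates | Power at 43 per arm | Needed per arm for 80% |
|---|---|---|
| 60% vs 40% | 46% | 97 |
| 50% vs 30% | 47% | 93 |
| 40% vs 20% | 53% | 82 |
| 50% vs 25% | 67% | 58 |

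**5. Cost of keeping several primaries.** Applying the step 1 formula at a split alpha:

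- two at 2.5%: 104 evaluable, and power at 86 falls to 71%
- three at 1.67%: 116 evaluable, and power at 86 falls to 65%

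One named primary at the full 5% leaves N = 86.

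**The case against.** The best defence is that the article calls the trial exploratory and a pilot, and that Section 2.9 words its test for severity only. A fair reader could conclude that severity is the intended lead outcome. That carries weight as to intent, but it does not designate an outcome. A stated alpha, a power calculation and two outcomes called primary remain unreconciled. It is also true that 5% would hold if all primaries had to succeed; the article states no such rule.

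Several stronger readings are tempting, and the documents do not support them:

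- **That the linear model inflates the error of the yes/no test.** It does not; that test stays near 5%.
- **That the yes/no outcome is constant at T0 by design.** T0 is measured again after screening, so some scores may fall to 33 or below. It is nearly constant.
- **That the linear model cannot give a risk difference.** Cell means of 0/1 data are proportions, so their contrasts are risk differences. The objection is one of fit: bounded data and almost no variance at T0.
- **That low power for case numbers is the model's doing.** It comes mainly from dichotomising the score, and logistic regression will not recover much of it.
- **That every repeat analysis is another route to success.** The article gives the repeats diagnostic purposes: to see whether change is driven by sleep alone, and to compare effect estimates between analysis sets. They should not be counted in the error rate.
- **That the PTCI is certainly a third primary.** The defining sentence lists two outcomes; the status of the PTCI is only unclear.

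**Conclusion.** The concern holds in a limited form. Two unranked primaries in Section 2.8.1 conflict with the single unnamed primary in Section 2.4. The family-wise error of 8.5–9.4% (about 12–13% with the PTCI) depends on success on any one outcome being enough, and on the simulation's assumed correlations and case rates. The direction follows from the text; the exact size does not.

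For the yes/no outcome the defect is a poorly suited model with a nearly uninformative T0 level, and an unstated power that is low under the assumed 20-point differences and still below 80% for 50% vs 25%. It is not a false-positive problem in that test. The plan should be corrected, and the change is one of wording.

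**What to change.** - **Section 2.8.1:** name PCL-5 total severity, with the full item set and analysed by intention-to-treat, as the single primary outcome. This fits Section 2.4, whose effect size comes from an earlier CBT-I trial's result on a PTSD symptom scale. Make probable PTSD and the PTCI secondary.
- **Section 2.4:** name that outcome where the text refers to the primary measure.
- **Section 2.9:** restrict the mixed general linear model to the continuous outcomes. Analyse probable PTSD at T1 and T2 by logistic regression with the T0 PCL-5 score as a covariate and no T0 outcome level, and report a risk difference.
- **Sections 2.8.1 and 2.9:** label the version without the sleep item and the per-protocol version as sensitivity analyses.

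Cost: wording only, with N = 86 unchanged. The downside is that probable PTSD, and the PTCI if it was meant as primary, lose primary status. Keeping two primaries with a split alpha would instead need 104 evaluable participants, or 104 / 0.8 = 130 recruited at 20% dropout. That figure rests on the continuous calculation and would still not secure power for the yes/no outcome.

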### Participants

2.3.

Participants aged between 18 and 55 years will be included in the study if they (1) have experienced a traumatic event within the past three months as measured with Life Events Checklist (LEC-5; Weathers et al., 2013) and show PTSD symptoms (PTSD Checklist for DSM-5 (PCL-5) score above cut-off value of 33) and (2) report on sleep disturbances which evolved or became stronger after the traumatic experience. Participants will be excluded from the study if they (1) take benzodiazepines or benzodiazepine receptor agonists, (2) report on a lifetime diagnosis of psychosis, bipolar disorder or more than two episodes of major depression, (3) have suffered from an alcohol or substance use disorder within the past year, (4) have an IQ < than 80 points, (5) are diagnosed with any systemic or neurological disorder (e.g. dementia), (6) show signs of acute suicidality, (7) are insufficiently able to communicate in German, (8) work in shifts or have had an intercontinental flight crossing two or more time zones within the past 30 days or (9) suffer from sleep apnea.

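### The stated 1-to-5 item coding of the PCL-5 does not fit the cut-off of 33 that governs entry and the probable-PTSD count

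*Protocol article*

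**What the plan says.** - **Item coding (2.8.1 Primary outcome measures).** Respondents rate each PCL-5 symptom on a "5-point likert scale (1 = not at all to 5 = extremely"). This is the only coding given in the article.
- **Primary outcome (2.8.1).** Beside symptom severity, the primary outcomes include the "number of participants with probable PTSD according to a PCL-5 cut-off of 33". The value is taken from a cited source and justified as giving the best balance of sensitivity and specificity for detecting PTSD.
- **Entry (2.3 Participants).** Eligible patients need a "PTSD Checklist for DSM-5 (PCL-5) score above cut-off value of 33".
- **Sleep item (2.8.1).** Because one PCL-5 item asks about trouble sleeping, "all analyses for the PCL-5 will be conducted with and without this item separately". No other cut-off is given for the shortened version.
- **Not stated.** The article gives no PCL-5 item count, no range of the total, no summing rule, and no coding on which 33 was derived.

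**The concern.** A cut-off on a sum score means something only on the coding for which it was derived. If every item starts at 1, a respondent with no symptoms already scores one point per item. The same 33 then marks a far lower level of symptoms than it does when items start at 0. A value put forward as the best discriminator for PTSD is hard to believe at a point where the average answer is less than one step above the lowest category.

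Two decisions hang on this number: who enters the trial, and who counts as a probable case afterwards. The first cannot be repaired at analysis, because patients admitted under a too lenient threshold are already randomised.

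**Working it through.** **The plan's own figure.** The 33 comes from a cited source and cannot be derived from anything in the article, so there is nothing to reproduce. The planned sample size does not depend on it.

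**Inputs.** From the article: items coded 1 to 5; cut-off 33; 86 participants required before the dropout allowance (2.4), that is 43 per arm. Assumed: the item count k, shown from 16 to 24.

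**Position of 33 on the scale.**
- Coded 1 to 5, the total runs from k to 5k, so 33 lies at (33 − k)/(4k) of the range.
- Coded 0 to 4, the total runs from 0 to 4k, so 33 lies at 33/(4k).
- The mean item rating at a total of 33 under 1-to-5 coding is 33/k.

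| Items (assumed) | Range, 1–5 | Points above floor | Position, 1–5 | Mean rating, 1–5 | Position, 0–4 |
|---|---|---|---|---|---|
| 16 | 16–80 | 17 | 26.6% | 2.06 | 51.6% |
| 17 | 17–85 | 16 | 23.5% | 1.94 | 48.5% |
| 19 | 19–95 | 14 | 18.4% | 1.74 | 43.4% |
| 20 | 20–100 | 13 | 16.3% | 1.65 | 41.3% |
| 22 | 22–110 | 11 | 12.5% | 1.50 | 37.5% |
| 24 | 24–120 | 9 | 9.4% | 1.38 | 34.4% |

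The two codings differ by exactly k points. With 20 items, 33 on 0-to-4 equals 33 + 20 = 53 on 1-to-5, and 33 on 1-to-5 equals 33 − 20 = 13 on 0-to-4.

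**Continuous severity.** Recoding replaces every total T by T + k. In the group-by-time contrast, (T1 − T0) in one arm minus (T1 − T0) in the other, k cancels. For a given set of participants the test of the first research question in 2.9 is identical under both codings.

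**Power for the count.** Assumptions: 20 items, normal totals with SD 15, treated mean 7.5 points lower, 43 per arm, two-sided 5% test of two proportions, and a case defined as 33 or more (half-point continuity correction). Control means are on the 0-to-4 scale.

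| Control mean | 0–4: control vs treated at ≥33 | Power | 1–5: control vs treated at ≥33 | Power |
|---|---|---|---|---|
| 20 | 20% vs 9% | 30% | 69% vs 50% | 44% |
| 25 | 31% vs 16% | 37% | 80% vs 63% | 40% |
| 30 | 43% vs 25% | 42% | 88% vs 75% | 34% |
| 35 | 57% vs 37% | 45% | 93% vs 84% | 27% |
| 40 | 69% vs 50% | 44% | 97% vs 91% | 20% |

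The share of cases rises in every row. Power falls at means of 30 and above and rises at 20 and 25.

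**Without the sleep item.** Going from 20 items to 19 with 33 unchanged moves the threshold from 16.3% to 18.4% of the range (1–5), or from 41.3% to 43.4% (0–4). A proportional cut-off is 33 × 19/20 = 31.35, so the difference is 33 − 31.35 = 1.65 points.

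**The case against.** The strongest reply is that the article does not contradict itself on its face. The item count and the coding behind 33 are not in it, and the phrase about 1 to 5 describes how respondents answer, not how totals are formed. It may be a slip of description while scoring runs on 0 to 4. This stands in part: a reader might infer that the trial is in fact scoring patients wrongly, and the document does not show that. It does not remove the point, because the article states one coding, and 33 sits low on that coding for every item count tried. Nor is this a detail left to an analysis plan: the coding is stated, and entry is decided at screening.

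A reader might also infer that hardly anyone could fall below 33 after treatment, so that the count could no longer show a difference. That does not follow. With a control mean of 35, 16% of treated participants still fall below 33; with a mean of 30, 25% do. A general loss of power does not follow either. A more lenient gate would admit milder patients and lower the means, and at means of 20 to 25 power is higher under 1-to-5 coding. The severity comparison is untouched by the recoding.

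On the sleep item, the article never says that 33 is kept for the shortened scale. That is an inference from the commitment to run all PCL-5 analyses both ways with only one cut-off given. The effect is small, and any fixed cut-off applies to both arms. The inequality point is also thin: 2.3 says above 33, 2.8.1 states no inequality, and at most one score point is at issue.

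**Conclusion.** The concern holds as a mismatch between a stated coding and a stated threshold. Under 1-to-5 coding, 33 lies in the lowest 9 to 27% of the range for 16 to 24 items, against 34 to 52% under 0-to-4; with 20 items the two readings are 20 points apart. If totals are summed as described, eligibility and the dichotomous primary outcome are much more lenient than intended.

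This rests on an assumed item count and on reading the described ratings as the scored values. Which of the two statements is wrong cannot be settled from the article. The continuous severity test is not affected, and no direction can be claimed for power on the count. The handling of the count without the sleep item is a secondary matter of about 1.65 points, assuming 20 items.

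**What to change.** - In 2.3 and 2.8.1, state the item count, item coding, total range and cut-off together, so that they agree.
- Check that the PCL-5 at screening and in the online survey at T0, T1 and T2 is scored on the coding for which the cited cut-off was derived.
- State one inequality and use it for both entry and outcome.
- For the version without the sleep item, either analyse the continuous score only, or pre-specify a cut-off scaled to the remaining items (about 31.4 if there are 20 items and the cut-off is 33).

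The cost is a wording correction and a check of the scoring. It needs no further patients and no further data.

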#### Secondary outcome measures

2.8.2.

Secondary outcome measures are (1) sleep quality measured by sleep diary entries (*Schlaffragebogen A*, SF-A/R; Görtelmeyer, 2011) filled in by both groups for 1 week around every time point, the insomnia severity index (ISI; Morin, 1993b), and the Pittsburgh Sleep Quality Index (PSQI; Buysse et al., 1989) including the addendum for PTSD (PSQI-A; Germain et al., 2005), a broader measure of sleep quality, that does not only include insomnia symptoms but also other symptoms that can occur in traumatized individuals, such as bad dreams and breathing problems during sleep, (2) depressive symptoms measured with the Beck Depression Inventory (BDI-II; Beck et al., 1996), (3) anxiety assessed with the Beck Anxiety Inventory (BAI; Beck et al., 1988) and (4) general functioning in everyday life quantified by the WHO Disability Assessment Schedule (WHODAS 2.0; Üstün et al., 2010). Sleep diary entries for measurement of sleep quality are additional and independent from the sleep diary included in the *somnio* program in the intervention group and the 8-week sleep diary planned as intervention for the control group. For pre and post measurement they are administered in the week before the intervention and the week after the intervention respectively to avoid any overlap with the sleep diaries during the intervention period.

All measures have shown to have good psychometric properties. For the PSQI, studies indicate high internal consistency (*α* = .75–.80) as well as moderate to high construct validity (Carpenter & Andrykowski, 1998; Hinz et al., 2017). For the BDI-II, internal consistency is described as around .9, the retest reliability ranges from .73 to .96 and it shows good sensitivity and specificity in detecting depression (Wang & Gorenstein, 2013). The BAI has high internal consistency (*α* = .92) and a test–retest reliability of *r*(81) = .75 over 1 week and discriminates well among different anxious groups (Beck et al., 1988). For the WHODAS 2.0, studies indicate high internal consistency ranging from *α* = .70–.97 in different populations and support reliability, validity, dimensionality and responsiveness of its German version (Pösl et al., 2007).

